**Methods:**

Fifteen individuals with mild traumatic brain injury and PPCSs will receive up to 12 weeks of interdisciplinary treatments including psychology, physiotherapy, and medical interventions. Primary feasibility outcomes including data on recruitment and retention rates and treatment adherence will be explored descriptively. The cognitive therapy rating scale will be used to assess treatment fidelity. A single-case series with multiple baseline design will be used to explore preliminary efficacy. Participants will be randomly assigned to baseline phases of 2, 4, or 6 weeks. Regarding patient-centred secondary outcomes, the Rivermead Post-Concussion Symptoms Questionnaire will be assessed three times a week during baseline and treatment phases. Secondary outcomes also include measures of mood, sleep and fatigue, physical functioning, return to activity, and health-related quality of life. Patient-centred outcomes will be assessed at baseline, pretreatment, post-treatment, and one- and three-month follow-up. Thematic analysis of participant experiences will be explored through qualitative interviews.

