It is clear that further scientifically rigorous work in this area is warranted to evaluate the feasibility and efficacy of interdisciplinary interventions, evaluate dosage, and identify factors that contribute to the effectiveness of such interventions. There is also a need to control for the effects of spontaneous recovery when evaluating the potential efficacy of treatments for concussion. Research trials may address this by establishing baseline rates of symptoms over time before the introduction of treatments. This pilot study, using a single-case series design with multiple baselines, therefore aims to pilot and conduct a preliminary evaluation of an interdisciplinary intervention that incorporates expertise from neuropsychology, physiotherapy, and medicine to target the primary factors thought to contribute to PPCSs. Using a single-case series experimental design principally enables the examination of the appropriateness of the trial design (e.g. choice of outcome and measurement, recruitment protocol, adherence to treatment manual) to inform the design of a subsequent definitive randomised controlled trial as well as enabling the evaluation of preliminary efficacy of this novel treatment.

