## Methods

### Study design

The study will use a single-case series with nonconcurrent multiple baseline A-B design across subjects with 1- and 3-month follow-up post-treatment to examine treatment efficacy and maintenance of gains. The current multiple baseline design will have three tiers, with participants randomly assigned to one of three baselines (2, 4, or 6 weeks) to maximise experimental control [104. ]. The trial will be run as five three-tiered trials to enable replication of trials for the evaluation of external validity [104. ]. The risk of bias in N of 1 trials scale (ROBiNT) and the single-case reporting guideline in behavioural interventions (SCRIBE) will be used to ensure methodological rigour and reporting [102. , 103. ]. Individual and group level data from the single-case studies will be used to examine the feasibility of the intervention to inform the trial design of a phase 2 randomised controlled trial.

We will also explore participant experiences of the intervention using semi-structured interviews and analyse this data using thematic analysis.

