##### Baseline phase

Once randomised and informed of length of baseline phase, participants will complete the RPQ three times a week on a Monday, Wednesday, and Friday. They will receive the RPQ as a REDCap link via email at 8:00 am and will receive a reminder email at 5:30 pm on the same day if they have not completed the RPQ. If participants do not complete the RPQ after the email reminder, they will be sent a follow-up text message reminder at 8:00 pm. If no response is made after the 8:00 pm reminder, this data point will be noted as incomplete.

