#### Treatment cessation

As part of the interdisciplinary treatment programme, clinicians will have ongoing communication with each other throughout the participant’s individualised treatment (communication between clinicians will be documented). Participants may be discharged from treatment early based on clinical opinion. They may be discharged from one discipline before the other (e.g. if physical issues resolve, they would be discharged from physiotherapy yet may continue psychological intervention to address persisting cognitive, mood, or behavioural issues).

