##### AIM 1: Feasibility of i-RECOveR

Data on recruitment and retention rates, protocol compliance, adverse events, treatments received, and treatment acceptability will be collected and analysed descriptively to inform guidelines for progressing the pilot trial to a larger phase 2 trial [25. ]. Adequate completion rates (i.e., 75%), limited adverse events, and signs of preliminary efficacy will inform whether the trial will progress to a randomised controlled design.

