##### AIM 2: Preliminary efficacy of i-RECOveR

**Post-concussion symptom severity**

Participant-reported post-concussion symptoms (RPQ) will be graphed to allow for visual inspection using GraphPad Prism 8. Systematic visual analysis will be conducted in line with established guidelines proposed by Spriggs, Lane, and Gast [101. ] and Lane and Gast [52. ], incorporating both within- and between-phase analyses to evaluate trend, level, and stability of data. Trend will be assessed using the split-middle method using median values [52. ].

Statistical analysis of single-case experimental data (i.e. total RPQ scores collected three times a week) will be conducted to augment visual analysis to provide more robust conclusions about the dataset. Planned comparisons between baseline and intervention phases will be conducted using the non-overlap method, Tau-U [68. ]. Tau-U is a nonparametric approach, appropriate for small data sets, which controls for improving trends (whether linear, curvilinear, or mixed) in the baseline phase and autocorrelation to generate an effect size [113. ]. An online Tau-U calculator (http://www.singlecaseresearch.org/calculators/tau-u) will be used to check for trend in the baseline, adjust for it where necessary, and calculate contrasts between phases [113. ]. This calculator will also be used to test omnibus statistics.

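### Tau-U's baseline-trend correction cannot provide the control of spontaneous recovery that the analysis plan credits to it, and no planned test uses the randomised stagger

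*Protocol article*

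**What the plan says.** The Introduction of the protocol article names the threat: "There is also a need to control for the effects of spontaneous recovery when evaluating the potential efficacy of treatments for concussion". Under Study design, the answer is a multiple baseline design with "participants randomly assigned to one of three baselines (2, 4, or 6 weeks) to maximise experimental control".

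Under AIM 2, Post-concussion symptom severity, the RPQ series is first assessed by systematic visual analysis of trend, level and stability within and between phases. Tau-U is then added to make the conclusions more robust. The section says that Tau-U controls improving baseline trends, whether linear, curvilinear or mixed, and also autocorrelation. The online calculator is used to "check for trend in the baseline, adjust for it where necessary, and calculate contrasts between phases" and to test omnibus statistics. No other statistical test of the RPQ series is described.

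Under AIM 1, completion rates, adverse events and efficacy feed the progression decision: "signs of preliminary efficacy will inform whether the trial will progress to a randomised controlled design".

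**The concern.** The trend correction in Tau-U subtracts a count of pairs within the baseline from a count of pairs between baseline and treatment. When treatment is much longer than baseline, the first count is small next to the second. A natural decline that runs on through treatment is then left almost intact in the corrected statistic.

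Tau-U also compares phases within one participant, and the omnibus value only averages those contrasts. Neither asks whether improvement follows the randomised start of treatment rather than time since entry. Yet the randomised start is the feature of the design that can tell the two apart.

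At stake is whether a significant omnibus Tau-U can be read as a sign of efficacy when the move to a randomised trial is considered.

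**Working it through.** **Inputs from the protocol article**
- Sampling rate: "participants will complete the RPQ three times a week on a Monday, Wednesday, and Friday" (Baseline phase). The Intervention phase section keeps the same schedule.
- Baseline length: "Participants will be randomly assigned to baseline phases of 2, 4, or 6 weeks" (abstract, Methods), so nA = 6, 12 or 18.
- Treatment length: participants "will receive up to 12 weeks of interdisciplinary treatments", so nB is at most 12 × 3 = 36. It can be less: "Participants may be discharged from treatment early based on clinical opinion" (Treatment cessation).
- Sample size: three tiers × five replications = 15, with at least five points per phase. Both reproduce, since 6, 12 and 18 all exceed five.

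**Assumptions.** The article gives no Tau-U formula, RPQ noise SD, autocorrelation, natural recovery rate or alpha. I use the usual form, Tau-U = (S_AB − S_A)/(nA·nB), with Var = (nA + nB + 1)/(3·nA·nB), inverse-variance pooling and a two-sided 5% level. Negative values mean improvement.

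**Step 1: ceiling on the correction.** S_A is at most nA(nA − 1)/2 pairs, and the contrast has nA·nB pairs. The share that can be removed is at most (nA − 1)/(2nB). The last two columns are for a noise-free steady decline from T1 with no treatment effect, at nB = 36.

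| nA | nA·nB | max S_A | max removed | corrected Tau-U | z |
|---|---|---|---|---|---|
| 6 | 216 | 15 | 0.07 | −0.93 | −3.6 |
| 12 | 432 | 66 | 0.15 | −0.85 | −4.4 |
| 18 | 648 | 153 | 0.24 | −0.76 | −4.5 |

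The variances are 43/648, 49/1296 and 55/1944, giving weights 15.07, 26.45 and 35.35 (sum 76.87). The omnibus over five participants per tier is −0.825, with z = −0.825 × √(5 × 76.87) ≈ −16. Full cancellation needs nB ≤ (nA − 1)/2, that is at most 2, 5 or 8 treatment points.

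**Step 2: shorter treatment, same decline.** At nB = 18 the corrected values are −0.86, −0.69 and −0.53. At nB = 9 they are −0.72, −0.39 and −0.06.

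**Step 3: with noise.** Simulated trials of 15 participants, assumed SD 5, nB = 36, lag-1 correlation 0 to 0.5, correction always applied, zero treatment effect. The table counts omnibus results significant for improvement, for which the nominal rate is 2.5%.

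| Natural fall per week | Significant omnibus |
|---|---|
| 0 | about 3–9% |
| 0.1 points | about 40–50% |
| 0.25 points | about 93–99% |
| 0.5 points | about 100% |

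- At 0.5 points per week the mean Tau-U is −0.43 uncorrected and −0.41 corrected, so the correction hardly matters. Applying it always or only when a baseline trend is detected gave the same picture.
- Single cases at 0.25 points per week are significant in about 19–31%.
- With six weeks of treatment for everyone, the omnibus is significant in 55–61% at 0.25 points per week and 89–99% at 0.5.
- The upper end of the flat-symptom range comes from autocorrelation. The variance formula has no term for it, so the claim to control it fails as well.

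**Step 4: alternatives.** A randomisation test permuted the 2/4/6-week lengths within blocks of three and compared six RPQs before the start with six after. It rejected in about 4–6% of null trials, and in about 100% with a 6-point immediate drop. A segmented regression with a linear time trend held its level under linear decline. Under decelerating recovery (6- or 12-point falls, half-lives of 4 or 8 weeks) it falsely signalled improvement in about 19–92%.

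**The case against.** The strongest reply is that the error needs recovery to be under way during the study. Entry requires symptoms that have persisted for at least a month and runs from 4 weeks to under 12 months after injury, so flat series are plausible. The article gives no recovery rate or RPQ variance. This stands, and it is why the rates are conditional. A reader might infer that the trial will show efficacy even if treatment does nothing. The documents do not support that.

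Second, 36 treatment points is a maximum, and the −0.93, −0.85 and −0.76 describe a noise-free monotone decline with no missed RPQs. This also stands. The problem remains at 18 points, however, and fades only near nine, and then mainly with the longer baselines.

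Third, a reader might infer that the plan has no guard against recovery. It has one: visual analysis comes first, and a trend that runs unbroken through the phase change is what it looks for. But it does not correct the omnibus p-value, which is meant to strengthen the conclusions.

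Fourth, efficacy is a secondary objective of a 15-person feasibility pilot. It is one of three considerations for progression, with no Tau-U threshold, and a later randomised trial would itself control for recovery. This limits the consequence but does not make the stated property of Tau-U correct.

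**Conclusion.** The point holds in a conditional form. The ceiling of 0.07, 0.15 or 0.24 on the correction follows from the protocol's own phase lengths and the usual Tau-U formula. The statement that Tau-U controls any improving baseline trend and autocorrelation is therefore wrong for this design.

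The false-positive rates rest on the assumed SD of 5, full-length treatment and the assumed rates of decline. A modest continuing decline of 0.25 points per week makes a significant omnibus result nearly certain without any treatment effect. With flat symptoms it is uncommon. Single-case conclusions are less affected.

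The design itself is not at fault. Its randomised stagger can separate an early treatment effect from recovery, but no planned statistical test uses it. The analysis text should be corrected before the data are analysed.

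**What to change.** 1. Delete the claim that Tau-U controls improving baseline trends of any shape and autocorrelation. Making the correction unconditional would not be enough.
2. Report per-case and omnibus Tau-U as descriptive effect sizes beside the visual analysis.
3. Base the group-level test on a start-point randomisation test that permutes the three baseline lengths within each block of three, giving 6^5 = 7,776 assignments. The article states block randomisation and five three-tiered trials but no block size, so the permutations must follow the procedure actually used.
4. Fix the window in advance, for example six RPQs before and six after each candidate start. This needs RPQs for 6 + 2 = 8 weeks from T1. A participant with a 2-week baseline must then contribute at least six weeks of treatment-phase RPQs. State a rule for series that end earlier and for missed RPQs. A 14-week window cannot be assumed for everyone, because early discharge is allowed.
5. Do not use a linear-trend segmented regression as the confirming test.

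The cost is analysis wording and a short script. No new data are needed unless the rule for short series calls for them.

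The downside is low power for effects that build gradually. Simulated tests using the first 14 weeks detected a 15-point effect growing over 12 weeks in only about 10–15% of trials. The short window does no better. Such an effect grows by 15/36 points per RPQ, so the contrast at the true start is 15 × 3.5/36 ≈ 1.5 points, while at a later, wrong start it is 15 × 6/36 = 2.5 points. The plan should therefore say that a non-significant result is not evidence against a slow-acting programme.

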**Secondary patient-centred outcomes**

Regardless of whether participants receive physiotherapy, psychological, or medical treatments beyond the three initial consultations, they will complete all secondary outcome measures according to an intention to treat analysis. GAS goals will be descriptively explored with any changes considered clinically significant [70. ]. Given this is a pilot investigation of the preliminary efficacy of this 12-week intervention, the focus for the secondary outcome measures will be on clinically significant change. Secondary outcome measures (BFI, FSS, ISI, DASS-21, IPQ-B, VOMS, BESS, SPNTT, flexion rotation, BCTT) will also be explored descriptively with 95% confidence intervals to explore clinically significant changes across the four assessment timepoints.

##### AIM 3: Qualitative analysis of participant experience of i-RECOveR

All participants will complete an interview using a semi-structured interview guide with the aim of producing an analysis of participants’ experience of the interdisciplinary intervention, exploring what elements they found helpful and those they found unhelpful, as well as exploring the impact(s) of the intervention on their symptoms and daily functioning. All interviews will be audio recorded. Recordings will be transcribed by author JN using NVivo software (version 12; [79. ]). An orthographic/verbatim notation system will be used as outlined by Braun and Clarke [12. ].

An inductive approach to analysis of the interview transcripts will be completed with codes derived from the data as per the six-phase thematic analysis approach outlined by Braun and Clarke [11. ]. The initial phase will require familiarisation of the data which will be undertaken during the interview and transcription stages. Following this, documentation of initial patterns and codes will be completed. The data will then be systematically recoded. Codes will then be categorised to produce themes and subthemes. Resultant themes will then be reviewed to ensure that they reflect the coded texts and are representative of the broader data set. Themes will then be defined and named before the manuscript is drafted. Regular investigator meetings, cross-checking of transcripts, codes, and revisions of themes will be planned to ensure rigour of the analysis.

### Ethics and dissemination

The trial has been registered with the Australian New Zealand Clinical Trials Registry (Trial ID: ACTRN12620001111965). Ethics approval has been obtained from the Monash University Human Research Ethics Committee (MUHREC number: 23005). Written parental consent and participant assent will be obtained for all participants aged 16 to 17. Written consent will be obtained for all participants aged 18 and older. Participants can withdraw from the study at any time. CBT, physiotherapy, and medical consultations have been demonstrated to be safe and tolerable for individuals with PPCSs. Although there are no known risks of participating in these interventions, it is possible that participants may find some of the content during the intervention difficult and/or emotionally challenging. The physiotherapy interventions may induce symptoms (e.g. dizziness), however, this will be done in a controlled environment under the care of trained physiotherapists. Research and clinical staff involved in the project are experienced in assessing and managing potential adverse events associated with this treatment and associated outcome measures should they arise.

Results from this study will be disseminated in peer-reviewed journals and will be submitted to local and international conferences. Given the study design, results could potentially be identifiable to those who know the cases well (e.g. doctors, family members). Identifying information will be limited as much as possible.

## Discussion

Persisting concussion symptoms after mTBI can disrupt return to education, employment, leisure activities including sport, social participation, and family relationships and can be a source of significant distress [1. , 16. , 17. , 38. , 82. , 88. ], requiring interdisciplinary support. Despite this, there are few studies worldwide evaluating interdisciplinary concussion interventions in adults, and evidence regarding the efficacy of these interventions is sparse. There is good indication that this may in fact be the best practice, but more evidence is required. In undertaking this research, we aim to first evaluate the treatment in a series of case studies and qualitatively evaluate participant experiences of the i-RECOveR treatment programme.

The results from this trial will inform the study design of a larger definitive phase-2 randomised controlled trial in the following ways:A fully powered randomised controlled trial of treatment for PPCSs has not been evaluated in an Australian context. Given this, there remains uncertainty regarding potential recruitment and retention rates. This trial will provide an opportunity to pilot the proposed recruitment strategy and make amendments if necessary to facilitate participant recruitment and engagement.Given that i-RECOveR is a new treatment, assessment of compliance (i.e. adherence and competency) to the treatment protocol is critical before progressing to a larger trial. By closely examining treatment recordings and compliance ratings, investigators will be able to identify areas of the manual that need further attention with regard to therapist training and supervision.Patient-centred outcomes will also be explored as part of this pilot investigation. It is hoped that this trial will serve to also inform the appropriateness of these measures for future trials as well as providing pilot data to inform the potential compliance rates associated with each measure. Given the study will use a robust single-case experimental design, signs of preliminary efficacy can be examined to explore whether proceeding to a phase-2 RCT is worthwhile.By undertaking qualitative interviews with participants in the pilot study, the end-user perspective of treatment will be elicited. It is anticipated that the responses will inform the unique experiences of i-RECOveR for each participant to identify aspects of the trial and treatment that worked or did not work. By understanding the end-user perspective, the pilot study will enable the adaptation of the treatment manual to better address the needs of individuals with PPCSs after mTBI.

The main trial will aim to assess the effectiveness of the intervention as well as providing insights into the participants’ experience of an interdisciplinary concussion intervention. Outcomes from this trial will be directly translated into the community. This research will evaluate treatments that are currently provided by the clinicians, with a focus on interdisciplinary management, and it is hoped that this project will eventually establish an evidence-based treatment programme for concussion.

### Trial status

Recruitment commenced in January 2021, and it is still ongoing.

## Data Availability

Not applicable.
